### 3.3. Potential Impacts of the Project

The aim of this protocol is to lay the foundations for a system capable of remotely monitoring the evolution of apathy in individuals with dementia and the associated impact on their caregiver. This system would provide a measure of behavioural markers of apathy that is completely independent of the patient’s self-report and thus not impacted by the patient’s subjective bias and anosognosia. Building on the knowledge acquired through this first ECOCAPTURE@HOME study, we expect that the following step of such a process will be to test a machine learning system which could, after a training period, automatically estimate the behavioural markers of apathy and the associated caregiver’s perception of the dyad’s status, using solely passive data from sensors. This system could present several interesting applications for clinicians and in particular neurologists. Firstly, this monitoring system could allow for the remote evaluation of the evolution of the patient-caregiver dyads’ psychological state, thus improving the potential for detection and prevention of dangerous situations such as caregiver burn out. Moreover, it could be used as a diagnostic tool providing information about a patient’s specific profile on the different behavioural markers of apathy and on how it is related with caregiver’s psychological status. This could prove useful for the implementation of new treatments adapted to a couple’s specific characteristics. In particular, by enabling the daily assessment of behavioural markers of apathy and associated dyad’s psychological health status, this system could be of great use to test and adapt therapeutic interventions accordingly in patients’ homes.

## 4. Conclusions

The ECOCAPTURE@HOME project focuses on the assessment of behavioural markers of apathy with an ecological approach in the everyday life context. It is characterised by three main innovative aspects: (1) the multi-modality of the assessment involving both passive and active data, with passive data combining measures from three sensors; (2) the focus on patient-caregiver dyads as a unitary system (instead of focusing exclusively on patients); (3) the possibility for concrete applications through the creation of a telemonitoring system allowing the remote follow-up of patient-caregiver couples and the identification of their specific characteristics and needs. The development of home-based therapeutic interventions targeting apathy could be highly facilitated using such a system.

## Figures and Tables

**Figure 1 ijerph-18-07824-f001:**
[figure not shown]
Methodological characteristics and applications of ECOCAPTURE studies. AD: Alzheimer’s disease; FTD: frontotemporal dementia (behavioural variant); PD: Parkinson’s disease; EDA: electrodermal activity; HR: heart rate.

**Figure 2 ijerph-18-07824-f002:**
[figure not shown]
Experimental design with two broad kinds of variables: (1) the behavioural markers of apathy (in green); (2) the caregiver’s perception of patient-caregiver status (in blue). EDA: electrodermal activity (or skin conductance); HR: heart rate.

**Figure 3 ijerph-18-07824-f003:**
[figure not shown]
Example of follow-up calendar for a patient-caregiver dyad. Sensors are worn by both patient and caregiver. Questionnaires are completed exclusively by the caregiver.

**Figure 4 ijerph-18-07824-f004:**
[figure not shown]
Summarised data flow during the 28-day follow-up.

**Table 1 ijerph-18-07824-t001:** Detailed description of visit 1.

Inclusion (35 min)	
5 min	After giving further information to the recruited couple on the objectives/conditions of the protocol and making sure that all is clearly understood, the investigator gives to both partners an information notice and collects their non-opposition to participate in the study. If a patient has a legal guardian, non-opposition is provided by the guardian and if a patient is under curatorship, non-opposition is provided by the patient with the help of their curator.
5 min	For all the participants, the collection of demographics (age, sex, and education level), medical history (in particular, date of first symptoms and diagnosis for patients) and treatments.
25 min	Verification of inclusion criteria including two tests: − For patients, MMSE: general cognitive efficiency − For all the participants, MADRS: depression symptoms.
**Assessment of the Severity of Dementia and of Clinical Symptoms of Interest (1 h)**	
30 min	For patients, Clinical Dementia Rating (CDR): severity of dementia symptoms in three domains (cognition, autonomy, behaviour).
30 min	For all the participants, − Apathy Scale (AS, self-reported version) − Dimensional Apathy Scale (DAS) − Epworth Sleepiness Scale (ESS).
**Handing over of the Equipment and Training (15 min)**	
15 min	Handing over two bracelets per couple; installation and configuration of a smartphone application for each partner for remote data collection; Training for the use of bracelets and application; for control dyads, random selection of the partner who fills the questionnaire (for active behavioural data) once a week; answering potential questions; Choice of a date for the first telephone conversation with the investigator during the 4-week remote follow-up.

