### 2.2. Population and Design of the Study

The ECOCAPTURE@HOME study is based on the recruitment of both patient-caregiver and control couples. Each dyad included in the study will be monitored through a multi-sensor wearable bracelet and questionnaires (on a smartphone application) for a period of 28 consecutive days. We plan to recruit a total of 60 couples between 40 and 85 years old divided into three groups: (1) Twenty patient-caregiver dyads with patients diagnosed with the behavioural variant of Fronto-Temporal Dementia (bvFTD), (2) Twenty patient-caregiver dyads with patients diagnosed with Alzheimer Disease (AD) and (3) Twenty healthy control dyads. Groups will be matched for age and socio-demographic characteristics.

The experimental design, summarised in Figure 2, is built upon the measurement model of the behavioural markers of apathy, presumed to predict the psychological status of the patient-caregiver dyad. Thus, we measure two types of variables on both a daily and a monthly scale:In all the dyads, the three theoretical behavioural markers of apathy: daytime activity level, quality of sleep, and emotional arousal, will be assessed using a pool of metrics extracted from the dyad’s raw passive and active behavioural data according to a hierarchical framework with three levels (raw data < metrics < markers considered as latent concepts);In patient-caregiver dyads only, the caregiver’s perception of the dyad’s psychological state is assessed by the following variables through questionnaires: (1) the patient’s level of apathy, as perceived by the caregiver; (2) the caregiver’s perceived burden; (3) the caregiver’s perceived quality of life.

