#### 2.4.2. Processing of Active Behavioural Data from Questionnaires

The questionnaire was completed once a week on a smartphone application and refers to five moments of the day: bedtime (3 items), wake time (3 items), breakfast (6 items), lunch (6 items), and dinner (6 items) (see Supplementary Materials, File S1 for further details on the item content of the questionnaire). In patient-caregiver dyads, these questions are completed by the caregiver who reports on the patient’s behaviour. Bed and wake time items will mostly allow to extract behavioural metrics related to the quality of sleep whereas mealtime items are used for the extraction of metrics associated with daytime activity and emotional arousal.

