#### 2.4.3. Metrics for Daytime Activity, Quality of Sleep, and Emotional Arousal

*Daytime activity*: After extracting the activity counts and distinguishing periods of wake and sleep from the acceleration signal, it is possible to calculate more elaborated metrics such as the mean number of activity counts per minute during daytime. We will also detect bouts of activity (sustained periods of elevated counts), bouts of sedentary time (sustained periods of low counts) and compute their mean frequency and duration during daytime. Using active data, we will assess the perceived partner’s investment in several activities at mealtimes: cooking, cleaning, washing the dishes, etc., which will also be useful as complementary daytime activity metrics.

*Quality of sleep*: After extracting the activity counts and distinguishing periods of wake and sleep from acceleration signal, metrics such as total sleep time, wake time after sleep onset, frequency, and duration of activity bouts during night-time will be extracted. We will also integrate metrics extracted from skin conductance and BVP signals during sleep as potential markers of the quality of sleep. The active data enable the calculation of additional metrics such as total time in bed (time between reported bed and wake times), sleep latency (time between reported bedtime and estimated sleep onset), difficulty to wake up and signs of fatigue for one of the dyad partners (patient in patient-caregiver dyads).

*Emotional arousal*: We will use metrics extracted from skin conductance and BVP signals. Metrics derived from the phasic parameter of skin conductance (GSRs) will enable the evaluation of emotional responses to short-term events (e.g., environmental stimulations). Metrics related to the variability of HR (HRV spectrum) are also considered as measures of emotional arousal. Active data will provide complementary metrics such as the perceived partner’s emotional response during interactions at mealtimes.

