### 2.7. Data Flow

All the information collected during Visit 1 will be registered using REDCap^®^ (version 10.9.4) secure web application. These data will be stored on the local secure server (of Paris Brain Institute, Paris, France).

During the 28-day follow-up, remote data collection will require two steps (see Figure 4):Collection of two types of data through an application installed (by the investigators) on patients’ and caregivers’ smartphones: data from sensors (passive behavioural data), and data from questionnaires (active behavioural data + caregiver’s perception of the dyad’s psychological state);Transfer of these data to a remote server application hosted by a local secure server (of the Paris Brain Institute).

Data from the sensors of the E4 bracelet will be continuously collected in both partners of the dyad and transferred to their smartphone application in real-time, each bracelet being paired with its carrier’s smartphone. In case of connection loss with the paired bracelet, the application will send a push notification to warn the participant. Data from questionnaires will be collected directly through the application, sending reminder notifications to the caregiver in patient-caregiver dyads (or to one of the partners, randomly selected, in control dyads).

After being encrypted, all the data collected by the application will be temporarily stocked on the smartphone and progressively transferred to the remote server application hosted by the local secure server. All the data collected by the application will be anonymised and identified only through the associated time-stamp and individual PIN code attributed to each participant of the study.

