Another potential measurement bias can be underlined in the assessment of behavioural markers of apathy through metrics from passive data of both individuals with dementia and their caregiver. Residual errors of prediction for the passive behavioural metrics aimed at measuring one behavioural marker will not be independent from each other and identically distributed: in particular, the residual errors relative to the caregivers’ metrics are likely to be covariates and so are the residual errors relative to the patients’ metrics. These covariances will have to be taken into account in the statistical modelling. It is also possible that the metrics extracted for both partners of one dyad are not sufficiently correlated to correspond to the measure of the same latent behavioural marker (especially for patient-caregiver dyads). If so, behavioural markers of apathy will need to be assessed using only the patient’s passive behavioural data instead of both the patient’s and caregiver’s passive behavioural data.

Finally, it seems difficult to estimate the extent of the measurement bias that might be introduced by the support provided to the caregiver through the study follow-up in an objective way. We could try to investigate a potential modification of signals from sensors worn by the caregiver between before and after a phone call with the investigator. However, we expect that this impact can be neglected (only two phone calls are scheduled with the investigator, and this is mostly for technical support).

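### Simple random choice of the reporting partner in control couples does not ensure that the control partner reported on resembles the patients in sex or age, which affects the daily-scale group comparison

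*Protocol article*

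**What the plan says.** **Who is reported on.** For patient dyads, Section 2.4.2 of the protocol article says that "these questions are completed by the caregiver who reports on the patient". For controls, Table 1 (equipment and training at visit 1) has "for control dyads, random selection of the partner who fills the questionnaire", and Section 2.7 repeats the rule for the reminder notifications: "or to one of the partners, randomly selected, in control dyads". No stratification of this choice is mentioned.

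**Matching.** Section 2.2 plans 20 bvFTD, 20 AD and 20 control dyads and states: "Groups will be matched for age and socio-demographic characteristics". It names neither sex nor the member of the dyad to whom the matching applies.

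**Where the reports are used.** Section 2.4 restricts the monthly scale to passive data; the daily scale uses passive and active data. Section 2.4.3 takes from the active data the partner's "investment in several activities at mealtimes: cooking, cleaning, washing the dishes" and similar tasks for daytime activity. It also takes time in bed, sleep latency, difficulty waking and fatigue for sleep, and response during mealtime interactions for emotional arousal. Section 2.8.2 compares mean marker scores between patient and control dyads on both scales. Section 2.1.1 makes separation of patient from healthy couples the first validity criterion.

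**Fallback.** Section 3.2 says that if the two partners' metrics correlate too weakly, "behavioural markers of apathy will need to be assessed using only the patient’s passive behavioural data". It does not say whose data would be used in a control dyad.

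**The concern.** The person described in a patient dyad is fixed by disease and brings the patient's own sex and age. The person described in a control dyad is fixed by a coin toss. Each mixed-sex couple contains one man and one woman, so matching couples on sex leaves open which of them stands opposite the patient. Matching couples on age settles the age of that person only as far as the partners are alike.

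If men and women differ on a reported metric, and the patients are not about half men, the patient-versus-control difference on that metric contains a sex component unrelated to apathy. If the patients are half men, chance imbalance among 20 controls still adds avoidable noise. Only one partner per control couple is ever reported on. The missing report on the other partner cannot be recovered, so after data collection the imbalance can be adjusted for but not designed away.

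**Working it through.** The protocol article gives no figure on this point. Its only power figure, 94.2% for model fit in Section 2.8.1, does not depend on who is reported on and is unaffected.

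**Inputs from the document**
- 20 control dyads and 40 patient dyads (20 bvFTD + 20 AD), Section 2.2.
- Simple random choice within each control couple, Table 1 and Section 2.7.

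**Assumptions, because the document gives no values**
- All 20 control couples are mixed-sex.
- Male share among patients, q: 50% to 80%, treated as fixed.
- Sex difference on a single reported metric, d: 0.5 to 1.0 SD.

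**Step 1: chance of a visible imbalance.** The number of men among the reported-on control partners is X ~ Binomial(20, 0.5). A gap of at least 20 points means |X − 20q| ≥ 4.
- q = 50%: X ≤ 6 or X ≥ 14, probability 0.115.
- q = 60%: X ≤ 8 or X ≥ 16, probability 0.258.
- q = 70%: X ≤ 10 or X ≥ 18, probability 0.588.
- q = 80%: X ≤ 12 or X = 20, probability 0.868.

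**Step 2: expected spurious difference on one metric.** The expected male share among the controls reported on is 0.5, so the expected shift is |q − 0.5| × d.

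| Patients male | Expected gap | Chance of gap ≥ 20 points | Shift at d = 0.5 SD | Shift at d = 1.0 SD |
|---|---|---|---|---|
| 50% | 0 points | 11.5% | 0 | 0 |
| 60% | 10 points | 25.8% | 0.05 SD | 0.10 SD |
| 70% | 20 points | 58.8% | 0.10 SD | 0.20 SD |
| 80% | 30 points | 86.8% | 0.15 SD | 0.30 SD |

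The table is symmetric: 40% male gives the same sizes as 60%.

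**Step 3: from metric to marker.** Section 2.8.1 assumes 36 metrics for three markers, 36/3 = 12 per marker on average. A marker score combines many metrics, so its shift is smaller than the table shows unless the other metrics carry a similar sex effect.

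**Step 4: scale against sampling error.** For 40 patient against 20 control dyads, the standard error of a mean difference is √(1/40 + 1/20) = 0.27 SD. Shifts of 0.05 to 0.20 SD are below one standard error; 0.30 SD, reached only at q = 80% and d = 1.0 SD, is slightly above it.

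**Step 5: which comparisons are reached.**
- Daily scale: reached, because active data on the reported-on partner enter the markers.
- Monthly scale: active data are excluded and passive data come from both partners. It is reached only if passive metrics are entered by role (patient slot, caregiver slot) or if the patient-only fallback is used. The same condition governs the passive metrics on the daily scale.

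**The case against.** A reader might infer that the random choice contradicts the matching statement, or makes matching impossible. The document does not support that. Section 2.2 promises matching of groups, not of roles, and does not name sex. Random choice balances sex in expectation if patients are about half men, and disturbs age little where partners are close in age. Nor does the article say when matching is carried out relative to the random choice; the full protocol may say more, and Section 2.6.3 uses an unexplained abbreviation for one control partner that suggests the role is defined elsewhere. These points stand: the supportable statement is that role-level likeness is not ensured.

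It is also fair that the household items are complementary metrics, that their wording is in a supplement not shown, and that their dependence on sex is an assumption. The fallback in Section 3.2 is conditional, and treating the reported-on partner as its control counterpart is an inference. The sizes are modest against sampling error. All of this limits the magnitude.

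Finally, age and sex are recorded for every participant (Table 1), so adjustment is possible, and a plan not shown may already include it. The absence of covariates from the article is therefore not the criticism. The point concerns a stated assignment rule. Adjustment with 20 controls only partly replaces balance that a different rule would give at the outset.

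**Conclusion.** The point holds in limited form. As stated, the selection rule does not ensure that the control partners reported on resemble the patients in sex, or in age beyond the likeness of partners. The certain reach is the daily-scale comparison, through the questionnaire metrics. It extends to passive metrics, including the monthly scale, only with role-wise entry or the patient-only fallback.

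For patients 50% to 70% male, the expected spurious difference on a single metric is 0 to 0.20 SD, and smaller on a diluted marker score. This rests on mixed-sex control couples, an assumed patient sex mix and an assumed sex effect of 0.5 to 1.0 SD. A reader should not conclude that the group comparison is invalid or that the monthly results are compromised. It is an inexpensive design improvement, worth making before control dyads are assigned.

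**What to change.** 1. In Table 1 and Section 2.7, replace simple random selection by stratified random selection of the reported-on control partner. The sex mix and, as far as possible, the age distribution of these 20 partners should be frequency-matched to the pooled 40 patients. One-to-one pairing is not available, because 40 patient dyads face 20 control dyads. Keeping a random element within strata still prevents couples from choosing their own reporter.
2. In Section 2.2, state that this partner is the control counterpart of the patient, and the reporting partner that of the caregiver. In Section 3.2, state that the same designation applies to the patient-only fallback.
3. Adjust the patient-versus-control comparison of marker means for the sex and age of the patient or reported-on partner.

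**Cost.** No extra visits or measurements; sex and age are already collected at visit 1. The one constraint is timing: control designation must run alongside or after patient recruitment, or use a target sex ratio that is updated as patients are enrolled.

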## Data Availability

Only study members at the Paris Brain Institute will have access to the full dataset once study data has been collected. Results will be disseminated via publications in peer-reviewed journals. There are no plans to grant the public access to the dataset or statistical code.

## Abbreviations

ACC: Anterior Cingulate Cortex; AD: Alzheimer’s disease; ADL: autonomy in activities of daily living; AS: Apathy Scale; bvFTD: behavioural variant of frontotemporal dementia; BVP: Blood Volume Pulse; CFA: Confirmatory Factor Analysis; CDR: Clinical Dementia Rating scale; DAS: Dimensional Apathy Scale; DLPFC: Dorsolateral Prefrontal Cortex; EFA: Exploratory Factor Analysis; ESS: Epworth Sleepiness Scale; fPCA: functional principal component analysis; GSR: Galvanic Skin Response; HR: Heart Rate; HRV: Heart Rate Variability; IBI: Inter-Beat-Interval; ICTs: Information and communication technologies; OFC: Orbitofrontal Cortex; MADRS: Montgomery-Åsberg Depression Rating Scale; MMSE: Mini-Mental State Evaluation; PD: Parkinson’s disease; SF36: Short-Form 36; VAS: Visual Analogue Scale; VMPFC: Ventromedial Prefrontal Cortex; ZBI: Zarit Burden Interview.
